#### mRNA expression

Pre-treatment and post-treatment mRNA expression will be measured using the NanoString PanCancer IO 360 Gene Expression Panel. This panel analyzes 770 genes and will be used to characterize mRNA expression in the tumor, tumor microenvironment, and immune response. Changes in gene expression signatures will be compared to the baseline biopsy in each patient to determine whether treatment with evorpacept (ALX148), cetuximab, and pembrolizumab reprograms the tumor microenvironment. The pre- and post-treatment biopsies will also be compared between patients that respond to treatment and patients that are refractory to treatment. Finally, baseline gene expression signatures will be correlated with response to treatment as a possible predictive biomarker.

## 8.3 ADVERSE EVENTS AND SERIOUS ADVERSE EVENTS

### 8.3.1 DEFINITION OF ADVERSE EVENTS (AE)

**Adverse event** means any untoward medical occurrence associated with the use of an intervention in humans, whether or not considered intervention-related (21 CFR 312.32 (a)).

### 8.3.2 DEFINITION OF SERIOUS ADVERSE EVENTS (SAE)

**Serious adverse event or serious suspected adverse reaction.** An AE or suspected adverse reaction is considered “serious” if, in the view of either the investigator or AGICC, it results in any of the following outcomes: death, a life-threatening adverse event, inpatient hospitalization or prolongation of existing hospitalization, a persistent or significant incapacity or substantial disruption of the ability to conduct normal life functions, a congenital anomaly/ birth defect, or other serious events that may jeopardize the patient and may require medical or surgical intervention to prevent one of the other listed outcomes. Important medical events that may not result in death, be life-threatening, or require hospitalization may be considered serious when, based upon appropriate medical judgment, they may jeopardize the patient or subject and may require medical or surgical intervention to prevent one of the outcomes listed in this definition. Examples of such medical events include allergic bronchospasm requiring intensive treatment in

an emergency room or at home, blood dyscrasias or convulsions that do not result in inpatient hospitalization, or the development of drug dependency or drug abuse.

In addition to the above criteria, AEs meeting either of the below criteria, although not serious per International Conference on Harmonization definition, are reportable to Merck in the same time frame as SAEs to meet certain local requirements. Therefore, these events are considered serious by Merck for collection purposes.

- Is a new cancer (that is not a condition of the study)
- Is associated with an overdose of pembrolizumab

### 8.3.3 CLASSIFICATION OF AN ADVERSE EVENT

#### 8.3.3.1 SEVERITY OF EVENT

The adverse event severity grading scale for the NCI CTCAE (v5.0) will be used for assessing adverse event severity. The following table will be used for assessing severity for adverse events that are not specifically listed in the NCI CTCAE (v5.0).

| Grade | Severity                                                                                                                                                                                                        |
|-------|-----------------------------------------------------------------------------------------------------------------------------------------------------------------------------------------------------------------|
| 1     | Mild; asymptomatic or mild symptoms; clinical or diagnostic observations only; or intervention not indicated                                                                                                    |
| 2     | Moderate; minimal, local, or non-invasive intervention indicated; or limiting age-appropriate instrumental activities of daily living a                                                              |
| 3     | Severe or medically significant, but not immediately life-threatening; hospitalization or prolongation of hospitalization indicated; disabling; or limiting self-care activities of daily living b,c |
| 4     | Life-threatening consequences or urgent intervention indicated                                                                                                                                                  |
| 5     | Death related to adverse event                                                                                                                                                                                  |

NCI CTCAE: National Cancer Institute Common Terminology Criteria for Adverse Events. Note: Based on the most recent version of NCI CTCAE (v5.0), which can be found at:

[http://ctep.cancer.gov/protocolDevelopment/electronic\\_applications/ctc.htm](http://ctep.cancer.gov/protocolDevelopment/electronic_applications/ctc.htm)

a Instrumental activities of daily living refer to preparing meals, shopping for groceries or clothes, using the telephone, managing money, etc.

b Examples of self-care activities of daily living include bathing, dressing and undressing, feeding oneself, using the toilet, and taking medications, as performed by patients who are not bedridden.

c If an event is assessed as a "significant medical event," it must be reported as a serious adverse event.

#### 8.3.3.2 RELATIONSHIP TO STUDY INTERVENTION

The clinician's assessment of an AE's relationship to study agent (drug, biologic, device) is part of the documentation process, but it is not a factor in determining what is or is not

reported in the study. If there is any doubt as to whether a clinical observation is an AE, the event should be reported. All AEs must have their relationship to the study agents assessed. In a clinical trial, the study product must always be suspect.

For all collected AEs, the clinician who examines and evaluates the participant will determine the AE's causality based on temporal relationship and his/her clinical judgment. The degree of certainty about causality will be graded using the categories below.

- **Definitely Related** – There is clear evidence to suggest a causal relationship, and other possible contributing factors can be ruled out. The clinical event, including an abnormal laboratory test result, occurs in a plausible time relationship to drug administration and cannot be explained by concurrent disease or other drugs or chemicals. The response to withdrawal of the drug (dechallenge) should be clinically plausible. The event must be pharmacologically or phenomenologically definitive, with use of a satisfactory rechallenge procedure if necessary.
- **Probably Related** – There is evidence to suggest a causal relationship, and the influence of other factors is unlikely. The clinical event, including an abnormal laboratory test result, occurs within a reasonable time after administration of the drug, is unlikely to be attributed to concurrent disease or other drugs or chemicals, and follows a clinically reasonable response on withdrawal (dechallenge). Rechallenge information is not required to fulfill this definition.
- **Possibly Related** – There is some evidence to suggest a causal relationship (e.g., the event occurred within a reasonable time after administration of the trial medication). However, other factors may have contributed to the event (e.g., the participant's clinical condition, other concomitant events). Although an AE may rate only as "possibly related" soon after discovery, it can be flagged as requiring more information and later be upgraded to "probably related" or "definitely related", as appropriate.
- **Unlikely to be Related** – A clinical event, including an abnormal laboratory test result, whose temporal relationship to drug administration makes a causal relationship improbable (e.g., the event did not occur within a reasonable time after administration of the trial medication) and in which other drugs or chemicals or underlying disease provides plausible explanations (e.g., the participant's clinical condition, other concomitant treatments).
- **Not Related** – The AE is completely independent of study drug administration, and/or evidence exists that the event is definitely related to another etiology. There must be an alternative, definitive etiology documented by the clinician.

### 8.3.3.3 EXPECTEDNESS

Expectedness will only be documented for SAEs. The medical monitor (in discussion with the study investigators) will be responsible for determining whether an SAE is expected or unexpected. An SAE will be considered unexpected if the nature, severity, or frequency of the event is not consistent with the risk information previously described for the study agent.

---

### **8.3.4 TIME PERIOD AND FREQUENCY FOR EVENT ASSESSMENT AND FOLLOW-UP**

The occurrence of an AE or SAE may come to the attention of study personnel during study visits and interviews of a study participant presenting for medical care, or upon review by a study monitor. All AEs including local and systemic reactions not meeting the criteria for SAEs will be captured on the appropriate eCRF. Information to be collected includes event description, time of onset, clinician's assessment of severity, relationship to study product (assessed only by those with the training and authority to make a diagnosis), and time of resolution/ stabilization of the event. All AEs occurring while on study must be documented appropriately regardless of relationship. All AEs will be followed to adequate resolution.

Any medical condition that is present at the time that the participant is screened will be considered as baseline and not reported as an AE. However, if the study participant's condition deteriorates at any time during the study, it will be recorded as an AE. UAPs will be recorded in the data collection system throughout the study.

Changes in the severity of an AE will be documented to allow an assessment of the duration of the event at each level of severity to be performed. AEs characterized as intermittent require documentation of onset and duration of each episode.

The PI will record all reportable events with start dates occurring any time after informed consent is obtained until 90 days after the last day of study treatment or until initiation of new treatment, whichever comes first. SAEs will be followed until resolution or stabilization. At each study visit, the investigator will inquire about the occurrence of AE/ SAEs since the last visit.

---

### **8.3.5 ADVERSE EVENT REPORTING**

The adverse event severity grading scale for the NCI CTCAE (v5.0) will be used for assessing adverse event severity as noted in Section 8.3.3.1. For each adverse event recorded on the Adverse Event eCRF, the investigator will make an assessment of seriousness, severity, and causality. Investigators will seek information on adverse events at each patient contact. All adverse events, whether reported by the patient or noted by study personnel, will be recorded in the patient's medical record and on the Adverse Event eCRF. Investigators should use correct medical terminology/concepts when recording adverse events on the Adverse Event eCRF.

Avoid colloquialisms and abbreviations. Only one adverse event term should be recorded in the event field on the Adverse Event eCRF.

After informed consent has been obtained but prior to initiation of study drug, only serious adverse events caused by a protocol-mandated intervention (e.g., invasive procedures such as biopsies, discontinuation of medications) should be reported. After initiation of study drug, all adverse events will be reported until 90 days after the last dose of study drug.

### **Adverse Events that are secondary to other events**

In general, adverse events that are secondary to other events (e.g., cascade events or clinical sequelae) should be identified by their primary cause, with the exception of severe or serious secondary events. A medically significant secondary adverse event that is separated in time from the initiating event should be recorded as an independent event on the Adverse Event eCRF. For example:

- If vomiting results in mild dehydration with no additional treatment in a healthy adult, only vomiting should be reported on the eCRF.
- If vomiting results in severe dehydration, both events should be reported separately on the eCRF.
- If a severe gastrointestinal hemorrhage leads to renal failure, both events should be reported separately on the eCRF.
- If dizziness leads to a fall and consequent fracture, all three events should be reported separately on the eCRF.
- If neutropenia is accompanied by an infection, both events should be reported separately on the eCRF.

All adverse events should be recorded separately on the Adverse Event eCRF if it is unclear as to whether the events are associated.

### **Persistent or Recurrent Adverse Events**

A persistent adverse event is one that extends continuously, without resolution, between patient evaluation time-points. Such events should only be recorded once on the Adverse Event eCRF. The initial severity (intensity or grade) of the event will be recorded at the time the event is first reported. If a persistent adverse event becomes more severe, the most extreme severity should also be recorded on the Adverse Event eCRF. If the event becomes serious, it should be reported to AGICC (i.e., no more than 24 hours after learning that the event became serious). The Adverse Event eCRF should be updated by changing the event from "non-serious" to "serious," providing the date that the event became serious, and completing all data fields related to serious adverse events.

A recurrent adverse event is one that resolves between patient evaluation time-points and subsequently recurs. Each recurrence of an adverse event should be recorded as a separate event on the Adverse Event eCRF

### **Abnormal Laboratory Values**

- Not every laboratory abnormality qualifies as an adverse event. A laboratory test result must be reported as an adverse event if it meets any of the following criteria:
- Is accompanied by clinical symptoms
- Results in a change in study treatment (e.g., dosage modification, treatment interruption, or treatment discontinuation)
- Results in a medical intervention (e.g., potassium supplementation for hypokalemia) or a change in concomitant therapy
- Is clinically significant in the investigator's judgment

It is the investigator's responsibility to review all laboratory findings. Medical and scientific judgment should be exercised in deciding whether an isolated laboratory abnormality should be classified as an adverse event.

If a clinically significant laboratory abnormality is a sign of a disease or syndrome (e.g., alkaline phosphatase and bilirubin 5x ULN associated with cholestasis), only the diagnosis (i.e. bile duct stenosis) should be recorded on the Adverse Event eCRF.

If a clinically significant laboratory abnormality is not a sign of a disease or syndrome, the abnormality itself should be recorded on the Adverse Event eCRF, along with a descriptor indicating whether the test result is above or below the normal range (e.g., "elevated potassium," as opposed to "abnormal potassium"). If the laboratory abnormality can be characterized by a precise clinical term per standard definitions, the clinical term should be recorded as the adverse event. For example, an elevated serum potassium level of 7.0 mEq/L should be recorded as "hyperkalemia."

Observations of the same clinically significant laboratory abnormality from visit to visit should only be recorded once on the Adverse Event eCRF.

### **Abnormal Vital Sign Values**

Not every vital sign abnormality qualifies as an adverse event. A vital sign result must be reported as an adverse event if it meets any of the following criteria:

- Is accompanied by clinical symptoms
- Results in a change in study treatment (e.g., dosage modification, treatment interruption, or treatment discontinuation)

- Results in a medical intervention or a change in concomitant therapy
- Is clinically significant in the investigator's judgment

It is the investigator's responsibility to review all vital sign findings. Medical and scientific judgment should be exercised in deciding whether an isolated vital sign abnormality should be classified as an adverse event.

If a clinically significant vital sign abnormality is a sign of a disease or syndrome (e.g., high blood pressure), only the diagnosis (i.e., hypertension) should be recorded on the Adverse Event eCRF.

### **Preexisting Medical Conditions**

A preexisting medical condition should be recorded as an adverse event only if the frequency, severity, or character of the condition worsens during the study. When recording such events on the Adverse Event eCRF, it is important to convey the concept that the preexisting condition has changed by including applicable descriptors (e.g., "more frequent headaches").

### **Hospitalization or Prolonged Hospitalization**

Any adverse event that results in hospitalization (i.e., inpatient admission to a hospital) or prolonged hospitalization should be documented and reported as a serious adverse event (per the definition of serious adverse event in Section 8.3.2), except as outlined below.

The following hospitalization scenarios are not considered to be adverse events:

- Hospitalization for respite care.
- Planned hospitalization required by the protocol (e.g., for study drug administration or insertion of access device for study drug administration).
- Hospitalization for a preexisting condition, provided that all of the following criteria are met:
  - The hospitalization was planned prior to the study or was scheduled during the study when elective surgery became necessary because of the expected normal progression of the disease.
  - The patient has not experienced an adverse event.
  - Hospitalization due solely to progression of the underlying cancer.

The following hospitalization scenarios are not considered to be serious adverse events, but should be reported as adverse events instead:

- Hospitalization that was necessary because of patient requirement for outpatient care outside of normal outpatient clinic operating hours.

### **Overdose or Error in Drug Administration**

An overdose is the accidental or intentional use of a drug in an amount higher than the dose being studied. An overdose or incorrect administration of study treatment is not itself an adverse event, but it may result in an adverse event. All adverse events associated with an overdose or incorrect administration of study drug should be recorded on the Adverse Event eCRF. If the associated adverse event fulfills seriousness criteria, the event should be reported to AGICC immediately.

### **Deaths**

Deaths that occur during the protocol- specified adverse event reporting period should be entered in the Adverse Event eCRF. All on-study deaths, regardless of relationship to study drug, must be recorded on the Adverse Event eCRF and immediately reported to AGICC.

Death should be considered an outcome and not a distinct event. The event or condition that caused or contributed to the fatal outcome should be recorded as the single medical concept on the Adverse Event eCRF. Generally, only one such event should be reported. The term "sudden death" should be used only for the occurrence of an abrupt and unexpected death due to presumed cardiac causes in a patient with or without preexisting heart disease, within 1 hour after the onset of acute symptoms or, in the case of an unwitnessed death, within 24 hours after the patient was last seen alive and stable. If the cause of death is unknown and cannot be ascertained at the time of reporting, "unexplained death" should be recorded on the Adverse Event eCRF. If the cause of death later becomes available (e.g., after autopsy), "unexplained death" should be replaced by the established cause of death.

During survival follow-up, deaths should be entered in the Adverse Event eCRF.

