21. Adverse Event (AE) Assessments: Adverse events should be documented and recorded at each visit using the National Cancer Institute Common Terminology Criteria for Adverse Events (NCI CTCAE) version 5.0. Patients must be followed for non-serious AEs from C1D1 up to 28 days after the last study treatment administration or until all drug-related toxicities have resolved, whichever is later; or earlier than 28 days should the patient commence another anticancer therapy in the meantime. For serious adverse events (SAEs), the active reporting period to AGICC or its designated representative begins from the time that the patient provides informed consent, which is obtained prior to the patient's participation in the study, ie, prior to undergoing any study-related procedure and/or receiving investigational product, through and including 28 calendar days after the last administration of the investigational product. SAEs experienced by a patient after the active reporting period has ended should be reported to the AGICC if the Investigator becomes aware of them, unless the SAE is attributed by the Investigator to complications of either the underlying malignancy or any subsequent anti-cancer therapy or to the patient's participation in a subsequent clinical study; at a minimum, all SAEs that the Investigator believes have at least a reasonable possibility of being related to investigational product are to be reported to the AGICC. To collect late immune related adverse event information, all patients will be contacted by phone 90 days after EOT. AEs will be collected continuously if there are changes between study visits.

22. Concomitant Treatments: all concomitant medications and Non-Drug Supportive Interventions should be recorded in the eCRF within 28 days prior to study entry (i.e., prior to C1D1). All concomitant medications taken during study participation will continue to be recorded continuously on the eCRF starting at the screening visit and ending 30 days after treatment discontinuation (See Section 6.6).

23. Tumor Tissue Samples: Patients in Cohort A will provide a fresh pretreatment biopsy sample and an

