#### **8.2.4 FINAL STUDY/TREATMENT DISCONTINUATION VISIT**

A final study visit is required if patients come off study for any reason. At least 28 days and no more than 35 days after discontinuation of treatment, patients will return to undergo the activities listed in Schedule of Events (Section 1.3), unless the assessment(s) were already completed within the prior week, or the last 6 weeks for the tumor response assessment.

Patients continuing to experience toxicity at this point following discontinuation of treatment will continue to be followed at least every 4 weeks until resolution or determination, in the clinical judgment of the Investigator, that no further improvement is expected. If the patient has any concern and contacts the clinic, the patient will be seen in the clinic within 5 calendar days of the patient’s contact with the clinic (assessments will be the same as the assessments performed at the Final Study/Treatment Discontinuation Visit).

---

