#### **8.2.5 AFTER TREATMENT / SURVIVAL FOLLOW-UP**

Overall survival information will be collected via telephone calls and/or clinic visits every 3 months  $\pm$ 14 days (first call and/or clinic visit to occur 3 months following the Final Study/Treatment Discontinuation Visit) until death, withdrawal of consent, the patient is lost to follow-up, study termination by AGICC, or a maximum of 2 years from the Final Study/Treatment Discontinuation Visit.

---

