### **Adverse Events After the Reporting Period**

After the end of the adverse event reporting period, all deaths, regardless of cause, should be reported through use of the Long-Term Survival Follow-Up eCRF. In addition, if the investigator becomes aware of a serious adverse event that is believed to be related to prior study drug treatment, the event should be reported through use of the Adverse Event eCRF.

---

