#### **9.4.4 SAFETY ANALYSES**

Safety will be assessed through summaries of adverse events. Adverse events will include changes in symptoms, changes in medical conditions, changes in vital signs, and changes in laboratory values. Additionally, separate summaries will be created which will include only serious adverse events (SAEs). When subjects experience multiple events of varying severity, the highest grade will be used in the subject-level summaries. Toxicity will be summarized and tabulated based on organ and severity.

---

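### Section 8.3.5 sends deaths in survival follow-up to the Adverse Event eCRF in one paragraph and to the survival eCRF in the next, so late disease deaths can be recorded as fatal adverse events at some sites and not at others

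*Protocol*

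**What the plan says.** All references are to the protocol.

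- **Section 8.3.5, Deaths.** Deaths inside the AE reporting period go on the Adverse Event eCRF. So do all on-study deaths, whatever their relationship to study drug. The condition that caused the death is entered as the event. The subsection ends: "During survival follow-up, deaths should be entered in the Adverse Event eCRF".
- **Section 8.3.5, Adverse Events After the Reporting Period.** Once the period is over, "all deaths, regardless of cause, should be reported through use of the Long-Term Survival Follow-Up eCRF". The Adverse Event eCRF is added "if the investigator becomes aware of a serious adverse event that is believed to be related to prior study drug treatment".
- **Length of the period.** Section 8.3.5: "After initiation of study drug, all adverse events will be reported until 90 days after the last dose of study drug". Section 8.3.4 also gives 90 days, but stops earlier if new treatment begins. Footnote 21 of the Schedule of Events (Section 1.3), repeated in Section 8.2.2, differs: "Patients must be followed for non-serious AEs from C1D1 up to 28 days after the last study treatment administration", or until drug-related toxicity resolves if that is later. The same footnote uses 28 days for active SAE reporting and exempts later SAEs that the investigator attributes to the underlying cancer.
- **Survival follow-up.** The final visit takes place "At least 28 days and no more than 35 days after discontinuation of treatment" (Section 8.2.4). Contacts then follow every 3 months ±14 days, with the "first call and/or clinic visit to occur 3 months following the Final Study/Treatment Discontinuation Visit" (Section 8.2.5), for at most 2 years from that visit.
- **Use of the data.** Safety and tolerability is secondary endpoint 6 (Section 3). Section 9.4.4 summarises adverse events, and "When subjects experience multiple events of varying severity, the highest grade will be used in the subject-level summaries".

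**The concern.** The first sentence of the Deaths subsection already covers deaths inside the reporting period. The sentence on survival follow-up therefore adds mainly later deaths, and those are the deaths that the next paragraph sends to another form.

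A site that follows the Deaths subsection would enter a colorectal cancer death a year after the last dose as an adverse event with a fatal outcome, which the severity table in Section 8.3.3.1 makes grade 5. A site that follows the next paragraph would enter the same death on the survival form only. In a multi-center trial, the recorded fatal-AE data would then depend partly on which paragraph a site applied. Section 9.4.4 takes the highest grade per patient, so one such entry would set that patient's worst grade unless the analysis removes it.

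**Working it through.** No power, alpha or sample-size figure bears on this point. The check is one of timing and wording, followed by an illustration of scale.

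**1. Do both instructions reach the same deaths?** Inputs: final visit at day 28 to 35 after treatment discontinuation (Section 8.2.4), first contact 3 months ±14 days later (Section 8.2.5), and AE reporting to day 90 after the last dose (Section 8.3.5). Three months is taken as 91 days.

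- Earliest first contact: 28 + 91 − 14 = day 105.
- Latest first contact: 35 + 91 + 14 = day 140.
- End of survival follow-up: 28 + 730 = day 758 to 35 + 730 = day 765.

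Discontinuation cannot precede the last dose, so counting from the last dose makes these times no shorter. Every scheduled contact falls after day 90, and therefore also after the 28-day cut-off in footnote 21. The exception is a patient whose period footnote 21 extends for unresolved drug-related toxicity. Between the final visit and day 90, a death lies inside the 90-day period and the Deaths subsection stands alone. From day 90 to about day 765, both instructions apply.

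**2. Can the two paragraphs be read together?**

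| | Deaths | After the Reporting Period |
|---|---|---|
| Late death, unrelated to drug | AE eCRF | Survival eCRF |
| Late death, believed related | AE eCRF | Survival eCRF and AE eCRF |

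The rows differ where it matters. If every late death went on the AE form, the condition about relatedness in the second paragraph would do nothing for deaths. The exemption in footnote 21 for late SAEs due to the cancer points the same way as the second paragraph.

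**3. Would removing the one sentence be enough?** No. The Deaths subsection also sends all on-study deaths to the AE form. Section 4.4 places the end of study at the 90-day call after the final visit, which is 28 + 90 = day 118 to 35 + 90 = day 125. Deaths between day 90 and that call could still be read as on-study and sent to the AE form. In addition, the cut-off itself has three versions (Sections 1.3/8.2.2, 8.3.4 and 8.3.5).

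**4. Scale, on assumptions only.** Assume exponential times, treatment stopping at progression, median OS of 6.4 to 8.8 months (regorafenib rows of Appendix 4), 6-month PFS of 20% to 40% (Section 9.2), and 51 to 60 treated patients (42 in Stage 2 plus 9 to 18 in Stage 1).

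- Mean OS = median / ln 2: 6.4 / 0.693 = 9.2 and 8.8 / 0.693 = 12.7 months.
- Mean PFS = 6 / (−ln S(6)): 6 / 1.609 = 3.7 and 6 / 0.916 = 6.5 months.
- Mean post-progression survival m = mean OS − mean PFS: 2.7 to 9.0 months.
- P(death 3 to 25 months after last dose) = exp(−3/m) − exp(−25/m) = 0.33, 0.57, 0.60 and 0.65 over the four combinations.
- Number: 0.33 × 51 ≈ 17 to 0.65 × 60 ≈ 39.

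A second proxy takes median OS minus median PFS from Appendix 4 (2.8 to 5.8 months) with 48 patients. It gives 48% to 65%, or 23 to 31 deaths. Either way, this counts deaths that fall under both instructions. It does not count deaths wrongly recorded.

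**The case against.** The best defence is that neither paragraph says only. A site that completes both forms breaches neither text, and the paragraph on events after the reporting period can be taken as the specific rule for later deaths. Survival follow-up also begins at the final visit, so the disputed sentence has a consistent use from then to day 90. This stands in part. It shows that a careful data manager could find a workable reading. It does not settle which reading applies: a site that completes both forms puts late disease deaths into the AE data, and a site that applies the specific rule does not.

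A reader might infer more, and the documents do not support it:

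- **Deaths lost to OS.** The second paragraph requires the survival form for every late death, and survival status is collected every 3 months. Nothing tells a site to use the AE form alone.
- **A fault in Section 9.4.4 for naming no time window.** That detail is commonly left to the statistical analysis plan, which is not at hand. A window there could keep late deaths out of the tables. Causality is also graded for each event, so unrelated deaths could be separated. Neither would correct the data-entry instruction.
- **A comparison of 17 to 39 deaths with the 0.4% and 0.8% drug-related death rates for pembrolizumab in Section 2.3.1.** One is an all-cause count under an ambiguous rule and the other is a drug-related rate, so they are different quantities.

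The count is also soft. Its low end pairs the lowest historical OS with the hypothesised PFS, and Section 4.1.2 allows treatment beyond progression.

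**Conclusion.** The contradiction is real and stands in the current text. After the AE reporting period, Section 8.3.5 names two different forms for the same deaths, and all scheduled survival contacts (about day 105 to 140 onward) lie beyond the 90-day cut-off. Late disease deaths can therefore be recorded as fatal adverse events at some sites and not at others, which makes the recorded fatal-AE data for secondary endpoint 6 inconsistent.

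The number actually affected is unknown and could be zero if sites are instructed uniformly. The 17 to 39 figure is at most an assumption-based count of deaths within reach of both instructions. The primary endpoint, the sample size, the tests and the stopping rule are not touched. The point is worth correcting because it feeds the safety record directly and the correction is nearly free.

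**What to change.** 1. In Section 8.3.5, Deaths, delete or correct the last sentence so that deaths after the AE reporting period go to the Long-Term Survival Follow-Up eCRF. An Adverse Event eCRF entry should be added only when the causal event is judged related to study drug.
2. In the same subsection, limit the sentence on all on-study deaths to deaths inside the AE reporting period.
3. Reconcile the length of that period across footnote 21 of Section 1.3 and Section 8.2.2 (28 days, or until drug-related toxicity resolves), Section 8.3.4 (90 days or new treatment) and Section 8.3.5 (90 days), so that one cut-off governs the routing. Which length to adopt is for the sponsor to decide.
4. Put the same rule in the form-completion instructions.

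The cost is a few edited sentences and one completion note, with no new patients and no new data collection. If late deaths have already been entered, a one-off review of those records would be needed.
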